## Abstract

**Background:**

The transition from childhood into adolescence can be considered as a critical developmental period. Moreover, adolescence is associated with a decreased use of adaptive emotion regulation strategies and an increased use of maladaptive emotion regulation strategies increasing the risk of emotional problems. Targeting emotion regulation is therefore seen as an innovative prevention approach. The present study aims to evaluate the effectiveness of Boost camp, an innovative school-based prevention program targeting ER, on adolescents’ emotion regulation skills and emotional wellbeing. Also secondary outcomes and possible moderators will be included.

**Methods:**

The aim is to reach 300 adolescents (16 class groups, 6 schools) in their first year of high school. A clustered Randomized Controlled Trial (RCT) with two conditions, intervention (*n* = 150) and control (n = 150), will be set up. Adolescents in the intervention condition will receive 14 lessons over the course of 2 days, followed by Booster sessions, and will be compared with adolescents in a non-intervention control group. The outcomes will be measured by self-report questionnaires at baseline, immediately after Boost camp, and at three and 6 months follow-up.

**Discussion:**

Data-collection is planned to be completed in May 2018. Data-analyses will be finished the end of 2018. The presented paper describes the Boost camp program and the clustered RCT design to evaluate its effectiveness. It is expected that Boost camp will have beneficial effects. If found effective, Boost camp will have the potential to increase adolescent’s ER and well-being, and reduce the risk to become adults in need. The trials is registered on the 13th of June 2017 in ISRCTN registry [ISRCTN68235634].

## Background

The transition from childhood into adolescence is a developmental period whereby young adolescents have to deal with a wide range of changes and challenges. First of all, this developmental phase is characterized by rapid physical and emotional development, which often coincides with higher levels of negative affect, and higher risk-taking behavior [27, 134]. Second, young adolescents are faced with growing academic expectations, while at the same time they report less school motivation, feel more pressured by schoolwork, and describe decreased perceived school performance [81]. Finally, early adolescence is associated with important social challenges, such as more complex and hierarchical peer relationships, which require refined social skills [135]. Hence, it comes as no surprise that this transition period often co-occurs with heightened levels of stress.

Parallel with the observed changes and challenges, adolescents also report more health complaints, less life satisfaction [81], and a sudden and massive increase in psychopathology symptoms [27]. Approximately 5 to 20% of the adolescents worldwide experience significant impairments due to psychological problems [146, 147]. Syndromes as drug abuse, anxiety, depression, and behavioral disorders show a clear increase in prevalence in early adolescence (i.e., 12 and 15 years) [35]. These findings are of great concern since mental health problems in adolescence are a clear predictor of serious psychopathology in adulthood [44, 146]. Furthermore, young adolescents with psychological problems often fail to find help and the majority of them (50–70%) does not receive (adequate) treatment [33, 34, 96]. It appears that adolescents are faced with various barriers that withhold them from seeking help, such as public, perceived, and self-stigmatizing attitudes to mental illness, general lack of knowledge about mental health service, and poor access to mental health services [24, 68]. The heightened risk for the development of psychological problems, the long-term burden of adolescent psychopathology, and the limited reach of treatment services highlight the importance of prevention and early intervention programs to prevent the development of psychopathology in adolescents [32, 33, 84].

### The role of emotion regulation

Prevention programs should tackle basic mechanisms involved in stress regulation. The transdiagnostic framework suggests that emotion regulation (ER) plays a crucial role in the etiology and maintenance of multiple psychological problems [63]. ER refers to the “processes by which individuals influence *which* emotions they have, *when* they have them and *how* they experience and express these emotions” [65]. In order to manage or modulate the intensity of the emotions experienced, various ER strategies can be used. ER strategies are considered adaptive or maladaptive dependent on their effects on affect and behavior in the long-term and their association with psychopathology [3, 23]. Adaptive ER strategies reduces negative affect and protect against the development of youth psychopathology. Examples are reappraisal, acceptance, distraction, and problem solving [115]. Maladaptive ER strategies are less effective in reducing negative emotion and are related with the development of psychological problems. Examples are rumination, avoidance, and suppression, [3].

Adolescence is known as an important and challenging phase with regard to ER development. First, young adolescents shift from external parent-guided ER strategies, such as support seeking, to internal autonomous ER strategies, such as cognitive reappraisal and problem solving [2, 53, 58]. Second, young adolescents experience more intense negative affect and ER difficulties originating in the different developmental courses between reactive and regulative cognitive brain systems, such as inhibition, working memory, emotional control and planning (defined as executive functions (EF)) [129]. Due to a slower maturation of the executive functions, young adolescents’ brain systems often shows an increased emotional reactivity but a slower activation of regulative cognitive processes when confronted with emotional stimuli [95, 129, 134]. This imbalance is also reflected in a decrease in the use of adaptive ER strategies and an increase in the use of maladaptive ER strategies among adolescents, specifically in 12-to-15-year olds [37, 69, 129, 150]. Both the underuse of adaptive ER strategies and the overuse of maladaptive ER strategies are associated with internalizing symptoms (i.e., depressive and anxiety symptoms) and externalizing symptoms in adolescence (i.e. attention-deficit/hyperactivity disorder and conduct disorder symptoms) [99, 117, 122]. These observations indicates that adolescence is characterized by an increased emotional instability [40, 129, 134], which may explain the increased risk of developing psychopathology in this age group.

Considering that adolescence is characterized by ongoing cognitive and emotional maturation [40, 129, 134], this developmental phase provides great opportunities for therapeutic interventions focusing on emotional wellbeing. Emerging research indicates that programs tackling stress regulation, developed within a transdiagnostic framework and integrating core components of evidence-based interventions (e.g. cognitive reappraisal, modifying action tendencies, prevention of emotional avoidance), have strong potential to improve adolescents’ emotional wellbeing, problem behavior, and academic performance, both in a prevention [36, 49, 51] and clinical context [20, 21, 30, 52, 108, 119, 130].

So far, results of school-based universal social and emotional prevention programs have been mixed, with some showing beneficial effects on competencies and attitudes of children and adolescents, whereas others did not [51]. There are several explanations for this equivocal result. First, adolescents are more eager to learn when programs are tailored to their needs. Consequently, prevention programs may have stronger effects during stressful life changes, such as the critical transition phase from childhood into adolescence or the start of secondary school [51, 55]. Second, up to date, there is no prevention program, exclusively targeting the basic underlying mechanisms related with wellbeing, imbedded in a strong evidence-based framework. Third, the majority of previous research only focuses on the effect on primary outcomes such as social-emotional skills and levels of emotional distress. However, also secondary outcomes are needed to fine-tune effects. For example, a subset of studies have showed positive effects of academic achievement as precursor of increased wellbeing later on [51], influenced by affective and cognitive functioning [70]. Yet, other crucial outcomes might be important to include as well like school drop-out and days absent [79], quality of peer relations [92, 118] and attitudes on mental health [19].

Finally, universal programs do not have the same effects on all participants. Therefore, it is necessary to identify subgroups of youngsters based on crucial variables such as EF, baseline scores on psychopathology, or gender, and explore which subgroups benefit less or more. For example, it is possible that adolescents with low levels of EF benefit less from a prevention program targeting solely ER, given the observations that skilled EF facilitates the learning of ER skills [28]. Furthermore, adolescents with psychological problems report greater declines in mental health after the stressful adolescents’ transition phase than peers without psychological problems [97]. Therefore, there is more room for improvement. In addition, it has been demonstrated that girls, compared with boys, experience the transition to adolescence differently and show a greater level of psychological distress in young adolescence [11, 31]. Therefore, it is possible that gender also influences the prevention program effects [136].

Taking into account the abovementioned concerns and findings, we developed ‘Boost Camp’, which is a 2-day universal prevention program targeting basic mechanisms involved in emotion regulation for young adolescents who recently made the stressful transition from primary to secondary school. It can be expected that improving adolescents’ ER skills will significantly increase emotional wellbeing [3, 116]. The present study will test the effectiveness by means of a clustered randomized controlled trial (RCT) on primary and secondary outcomes, with long-term follow-up assessments at 3 and 6 months follow-up, taking into account important moderators.

### Goals and hypotheses

The present study has three main goals. First, this study will test the effectiveness of a new school-based universal prevention program “Boost Camp”, targeted at strengthening ER skills in the stressful first year of high school. It is hypothesized that Boost Camp will improve or maintain emotional wellbeing. More specifically, it is hypothesized that Boost Camp will lead to an *increased* use of adaptive ER, *more* positive affect, a *higher* self-esteem, and a *better* quality of life in participants in the intervention condition compared with adolescents in the control condition. Moreover, *less* negative affect, *less* use of maladaptive ER and *less* depressive and anxiety symptoms will also be seen as markers of wellbeing.

Second, this study will test the effects of the program on secondary outcomes. It is hypothesized that Boost Camp will lead to *better* peer relations, *less* negative mental health attitudes, an *increase* in academic achievements, a *smaller* amount of school absenteeism and *less* school drop-out. Third, this study will examine the moderating role of child characteristics such as EF, baseline level of psychological problems, and gender. It is hypothesized that the program will be *less* effective for young adolescents with lower levels of EF and *more* effective for young adolescents with a higher baseline level of psychological problems. Finally, due to the difference in experiencing difficulties and psychological distress within the transition phase, the program is expected to have better effects for girls than for boys.

## Methods

### Participants and procedure

Six secondary schools in the East of Flanders are contacted to participate in the study. Participants are adolescents in their first year of secondary school (7th grade, ages 11–13). The aim is to reach 300 students spread over 16 classes. We ensure the inclusion of students from different Socio Economic Status (SES) groups and various educational levels to compose a heterogeneous sample. In Belgium, there are two educational levels in secondary school. The first education level, grade A, is considered as a broad first grade in which students receive basic knowledge on technics, mathematics, or languages, with the intention to prepare them on a more specific educational program in the second grade. The second education level, grade B, is intended for students with specific needs. Both are included.

Schools that are interested are asked to participate with as many first-grade class groups as possible. If they give their consent to take part in the study, they are randomized by the researcher in a intervention or a control group. Finally, six rural schools with comparable background and meeting the same language criteria decided to participate in the study. All schools receive information letters for students and their parents, which contain detailed information about the study aims and procedure. Parents can either give or withhold their permission for including their child’s data in the study, and both parents and children are free to withdraw from the study at all times. The Boost Camp program is incorporated in the class curriculum, so all participants in the intervention condition receive the program. The advantage of incorporating the program in the class curriculum is that all adolescents participate and interact. To ensure that the intervention and the control schools place an equal emphasis on students’ mental health, teachers of all participating schools receive a workshop on care management and are invited to sign a school charter on the importance of emotional well-being of the schoolchildren.

In the intervention condition, students receive the 2-day prevention program Boost Camp followed by two extra Booster sessions. Boost Camp takes place in the beginning of the new school year, between the last week of September 2017 and the first week of October 2017. The booster sessions will be provided in the first (December 2017) and the second semester (April 2018). In the control condition, students participate in the regular school programs.

Participants will fill out online questionnaires anonymously, by using random assigned participants codes, during school hours four times throughout the first year of secondary school (Baseline, post, 3FU, 6FU). Each questionnaire session will take approximately two school hours (100 min) and will be supervised by the classroom teacher and a research assistant. Teachers and parents of participants will be asked to fill out questionnaires at two times, at the beginning (September 2017) and at the end (May 2018) of the school year. Participating classes will be rewarded with a photoshoot.

The Ethical Committee of the Faculty Psychology and Education Sciences of the Ghent University has approved the study design and data collection. Furthermore, all data collection procedures are performed in accordance with the national laws and the 1964 Declaration of Helsinki and its later amendments. During the research, any data gathered will be stored and be accessible by the primary researcher as stated in the Data Management Plan. Digital files (i.e. online questionnaires) are stored on the primary researcher’s personal computer drive, which requires a password. In addition, sensitive data (i.e. contact information) will be stored in a separate file that requires an additional password to open. Non-digital documents will be stored save in the faculty archives. Sharing a file containing personal information is out of the question.

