### Design

The effectiveness of Boost Camp will be tested by a clustered randomized controlled trial (cRCT) with two conditions, e.g. an intervention and a control condition (see Fig. 1). Randomization is clustered by school, which reduces the risk of contamination.

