### Data analysis

Power analyses were calculated to determine the required sample size for detecting a clinically significant difference between the intervention and control group at 6 months follow-up on one primary outcome (FEEL-KJ). With a significance level of α = 0.05 and a power level of β = 0.90, a total sample of 86 N_Non-cluster_ participants is needed to detect a significant difference. However, the clustering of participants within schools has to be considered and therefore, the design effect is calculated as 1 + (m-1)*ICC, with m referring to the number of participants per cluster [57]. Based on prior research determining the ICC values for adolescent health outcomes [121], an Intraclass Correlation Coefficient (ICC) of 0.02 was used. The estimated average size of the classes participating in current study is counted on 20 students per class, resulting in a design effect of 1,38. Moreover, as the intervention requires a high time investment, an 3:2 ratio in favor of the control group will be chosen at randomization. Following the recommendations of Gao et al. [57], the final calculation of the total sample of the control group was multiplied by the design effect with the randomization ratio and the N_Non-Cluster,_ resulting in a total sample size of 241 students, 145 for the control group and 97 for the intervention group. Taking into account declined participation and loss to follow-up, a drop-out rate of 20% is estimated. Finally, this resulted in a required sample size of 291 students, 174 in the control group and 117 in the intervention group, clustered in at least 16 classes.

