However, some limitations of the present study can be identified as well. First of all, the randomization at school-level increases the risk of different participants characteristics, like social economic status, which in turn decreases the chance to create a perfectly matched and equivalent control group and increases the risk of selection bias [80]. Furthermore, there is no active control group used, because up until now, there is no other existing Dutch school-based ER prevention program to which Boost Camp could be compared. Second, emotional wellbeing is only assessed by self-report measures which includes possible response biases through social desirability or a lack of introspection [6]. Finally, participants and trainers were not blind to the allocated intervention, through which it is possible that adolescents in the intervention condition try harder to be aware and effective regulating their emotions, which is known as the Hawthorne Effect [80]. However, educational research trials often lack blinding as a design feature due to the high visibility of the interventions. Moreover, other evaluation methods cannot improve this because they also will not operate blinding [80].

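### Schools are randomised once the school consents, and nothing places parental permission or baseline before families know the arm, so inclusion and baseline answers can depend on it

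*Protocol article*

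**What the plan says.** The Design section makes the school the unit of allocation: "Randomization is clustered by school, which reduces the risk of contamination". In Participants and procedure, the trigger for allocation is the school's own agreement: "If they give their consent to take part in the study, they are randomized by the researcher in a intervention or a control group".

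The same paragraph then turns to families. "All schools receive information letters for students and their parents, which contain detailed information about the study aims and procedure". After that: "Parents can either give or withhold their permission for including their child’s data in the study". The programme is part of the curriculum, so every pupil in an intervention school receives it and the parent decides only about the data.

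The Data analysis section makes one allowance for refusal and loss together, not split by arm: "Taking into account declined participation and loss to follow-up, a drop-out rate of 20% is estimated". Strengths and limitations states that "participants and trainers were not blind to the allocated intervention". It also accepts a risk of selection bias from randomising schools, which it ties to differing participant characteristics such as socio-economic status. It does not mention permission given with knowledge of the arm.

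**The concern.** In a cluster trial, randomisation balances the clusters. It protects the comparison of individuals only if entry into the analysed sample does not depend on the allocation. If parents know the arm when they decide, the two arms can include different kinds of pupils, and no property of the school randomisation corrects this.

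Knowledge of the arm changes the setting of the decision. In an intervention school, the child will attend the two-day camp either way. In a control school, what the study brings to the pupil is mainly four questionnaire sessions of about 100 minutes each.

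The T0 answers are exposed too. The camps run from the last week of September 2017, and pupils who expect one within weeks may answer T0 differently. T0 is the baseline adjustment in the mixed model, and baseline differences also decide which further covariates enter. All primary outcomes are self-reported.

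**Working it through.** **The order of steps.** The table sets out what the article fixes and what it leaves open.

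| Step | What is stated | Date or order stated? |
|---|---|---|
| School consents | Precedes that school's randomisation | Order yes, date no |
| School randomised by the researcher | Follows school consent | No date |
| Letters to families | Go to all schools | No |
| Parental permission for data | Described after the randomisation sentence | No |
| T0 | Beginning of the school year, before the camp | Relative to the camp yes; relative to disclosure of the arm no |
| Camp | Last week of September to first week of October 2017 | Yes |

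Only the first link, school consent before school randomisation, is explicit. That permission comes later is an inference from the order of the account. No entry places permission or T0 before the arm is known to families.

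**Size of the risk.** The article gives no figure for this, so there is none to reproduce. Two assumptions are needed: the refusal fraction p in each arm, and a gap of 0.5 SD in wellbeing between decliners and others. The result depends on what the gap is measured against.

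(a) Gap between decliners and consenters. The shift in the included mean is p × 0.5.
- 10% against 2%: 0.050 − 0.010 = 0.040 SD
- 20% against 5%: 0.100 − 0.025 = 0.075 SD

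(b) Gap between decliners and all eligible pupils. The shift is p × 0.5/(1 − p).
- 10% against 2%: 0.056 − 0.010 = 0.045 SD
- 20% against 5%: 0.125 − 0.026 = 0.099 SD

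The illustrative range is therefore 0.04 to 0.10 SD before baseline adjustment.

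**What this does to the test.** Inputs from the Data analysis section are the design effect 1 + (20 − 1) × 0.02 = 1.38, which agrees with the stated 1.38, and arm sizes of 145 and 97. On a standardised outcome, SE = √[1.38 × (1/145 + 1/97)] = 0.154 SD. With no true effect and a two-sided 5% test, the type I error is:

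| Bias (SD) | Type I error |
|---|---|
| 0.04 | 0.058 |
| 0.05 | 0.062 |
| 0.10 | 0.100 |

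These are also before baseline adjustment, which would remove part of the bias. It would remove less if the T0 answers were themselves shifted by knowledge of the arm; that effect cannot be sized from the document.

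**The case against.** The strongest reply is that the sequence is not stated. The paragraph is not strictly chronological: the sentence after the randomisation step reports that six schools finally decided to participate, which must have come first. Letter content and the timing of disclosure are also matters that a condensed article may leave to the full protocol. This stands in so far as the article does not show that permission followed allocation. It does not remove the point, because the article does fix school consent alone as the trigger and discusses selection bias without this route.

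Three stronger readings are tempting and are not supported.
- A reader might take the blinding sentence to mean that parents knew the arm when giving permission. It concerns participants and trainers, and goes on to pupils trying harder under the intervention; it says nothing about the moment of permission or T0.
- A reader might take the 20% allowance to show that refusals come from pupils already allocated. Refusals before allocation fit the wording equally well.
- A reader might assume that the letters differ by arm. They are described without distinction, which neither shows nor excludes this.

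The mechanism is also weaker than usual. Withholding permission does not take a child out of the programme, and control pupils are asked for the same questionnaires in the same period, so refusal may differ little between arms. This stands and limits the likely size.

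The article also argues that other evaluation methods could not supply blinding. That may hold for delivery of the camp. It does not hold for permission and T0, which can be completed before the arm is announced.

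**Conclusion.** The point holds as an open and avoidable risk. School consent triggers randomisation, parental permission is described afterwards without a date, and nothing places permission or T0 before families and pupils know the arm. Inclusion and baseline answers can therefore depend on the arm. The article does not show that they did.

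The likely effect is small: 0.04 to 0.10 SD before baseline adjustment, with type I error of about 0.06 to 0.10. These figures rest entirely on the assumed refusal rates and the assumed 0.5 SD gap. The upper end is deliberately unfavourable, since 20% refusal in one arm uses up the protocol's whole allowance for refusal and follow-up loss. If permission and T0 did precede disclosure, one sentence saying so would settle the matter.

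**What to change.** Use the same arm-neutral information letter in all six schools. Fix the list of participating classes in each school before randomisation. Complete parental permission and T0 before the allocation is announced to parents and pupils, and state this order in the procedure. Principals, and teachers where scheduling requires it, may be told earlier.

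If this is no longer possible, report eligible, refused and included pupils by school and arm. Add a sensitivity analysis, for example one that moves the estimated effect by the observed difference in refusal rate multiplied by a range of assumed decliner–consenter gaps, and report the gap at which the conclusion would change. Name this route of selection bias in the limitations.

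The cost is the wording of one letter and the order of steps in September 2017, with no extra staff or visits. The downside is a short window before the camps during which schools must withhold the allocation from families. Teachers supervise the T0 sessions and must release two curriculum days, so those told early have to keep the arm from their pupils until T0 is done.
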